**Fig. 2 Fig2:**
[figure not shown]
Conceptual framework of Aim2Be

#### Aim2Be features

Aim2Be is not a prescriptive app, but instead, it utilizes strategies to activate self-regulatory skills through a self-guided journey of self-discovery of current health behaviors and autonomy to select which health behaviors the user wants to work on. Strategies employed by the various app features are grounded in Michie’s behavior change taxonomy, which specifies the “active ingredients“ of behavior change interventions [47]. Children will be subdivided into two versions of the app based on their age: teens (13–17 years old) and preteens (10–12 years old) and will be able to select which aims they wish to address. Once an aim is selected, teens start a stage, and preteens start the aim as a whole, and then are provided tasks to help them set incremental goals, plan, and self-monitor their behaviors. In the application environment, the users progress along their journey by completing games, tasks, and activities including quizzes. The user receives currency that they can use to unlock collectibles and “choose your own adventure” stories. Users are provided with tools within the app to further support their journey including Check-Ins, Quick Wins, Articles, Quizzes, and a moderated Social Wall with daily topics to help engage users. Features that are incorporated in the preteen, teen, and parent apps, as well as the BCT [47] targeted by these features, are summarized in Table 1.

**Table 1 Tab1:** Summary of Aim2Be© features and behavior change techniques

App feature	Description	Behavior change taxonomy [47]
Gamification components		
Profile/Onboarding *PT, T*	After a user creates an Aim2Be account, the user can play the game, “What animal are you?” The game involves answering a variety of questions about the user’s preferences, with various question formats. For example, users might be asked whether they prefer spending time with people or spending time alone. At the end of the game, the user is presented with an animal avatar recommendation (e.g., lynx, tiger, panda, etc.) along with adjectives describing that identify profile (e.g., “wild, determined, unafraid, intelligent, & habitual”). The users are given the option to select a different animal avatar, if they wish, to represent them in the app and the option to further customize their animal avatar, by selecting clothes and accessories.	13.4 Valued self-identity
Daily Bonus *PT, T*	Each time a user opens the app, the user is invited to break a piñata from which extra currency can be gained.	10.2 Material reward (behavior)
Quick Wins *PT, T, P*	Each day, a new Quick Wins appear on a side bar of the users home page. Quick Wins are quick, simple, and straightforward tasks that prompt the user to do something positive for their health that day (e.g., “Stand up. Shake it out. Stretch. Reach up to the sky, then to the floor.”) or to encourage them to explore a new aspect of the app (e.g., “Check out Aimbot for help.”). Users earn currency dollars for each day they complete a Quick Win.	4.1 Instruction on how to perform a behavior
		8.1 Behavioral practice/rehearsal
		8.2 Behavior substitution
		8.3 Habit formation
		8.4 Habit reversal
		8.7 Graded tasks
		10.4 Social reward
Quizzes *PT, T*	Users can complete short quizzes within the app. Whether the user selects the correct or incorrect answer, a pop up appears after each question with an explanation of the correct answer. Users earn currency diamonds for each quiz they complete.	2.2 Feedback on behavior
		4.2 Information about antecedents
		5.1 Information about health consequences
		5.3 Information about social and environmental consequences
		5.6 Information about emotional consequences
		6.2 Social comparison
Currencies *PT, T*	Users collect currency dollars and currency diamonds for engaging with different components of the app. These currency dollars and diamonds can be used to purchase collectibles and stories, respectively.	10.2 Material reward (behavior)
Collections *PT, T*	Collections include a variety of virtual items (e.g., skateboard, phone, lipstick, sneakers, etc.), divided by level, that a user can purchase with a certain number of currency dollars.	10.2 Material reward (behavior)
Stories *PT, T*	Users can use their currency diamonds to purchase interactive and/or engaging stories. Each story is divided into multiple chapters that are “unlocked” as a user reaches a new level.	10.2 Material reward (behavior)
	Stories present users with a fictional situation and character who is faced with a series of decisions. Users guide the fictional character through the situation by making decisions in a choose-your-own-adventure format. A recent study suggests that when individuals “lose themselves” in the world of a fictional character, they change their own behavior and thoughts to match that of the character. This phenomenon has been termed experience-taking [48]. Stories are designed such that users will empathize and identify with the fictional characters, allowing them to have experiences that they may not have yet had the chance to encounter in their regular lives. This allows them to shift their self-perception to include their “new experiences” and begin to identify themselves as the type of person who chooses healthy patterns of action.	9.3 Comparative imagining of future outcomes
		16.1 Imaginary punishment
		16.2 Imaginary reward
		6.1 Demonstration of behaviors (symbolic role modeling)
Behavioral Components		
Aim *PT, T, P*	Aims are high-level goals that users can choose to pursue, such as “Be sugar smart.” Users may pursue one aim at a time or may pursue up to three aims concurrently.	1.3 Goal setting (outcome)
		1.4 Action planning
	Once a user selects an aim to pursue, the user is first asked to indicate why they selected the aim, by completing the sentence, “I want this because....” Next, the user is asked to indicate on a Likert scale the importance of the aim, and their confidence in being able to achieve it. Following this, the user is asked to note any obstacles they might face in working toward the aim. Lastly, the user is asked to adopt a time frame for achieving their aim; they can either accept a recommended time frame or create a custom time frame.	1.6 Discrepancy between current behavior and goal
		1.9 Commitment
		13.5 Identity associated with changed behavior
	Users also have the option to request support from their parent or guardian or from a peer. Users can write their specific needs related to tasks and aims and send these to their desired recipient in email form through the application.	
	Users are given daily tasks related to the aim they set and are congratulated and awarded currency as they complete tasks and stages. When an aim is completed (all the tasks have been accomplished), the aim is moved to the “Completed aims” folder.	
Stage *T, P*	Aims consist of several stages that break the high level goal into more focused components. For example, the aim “Be sugar smart” includes the stages “Be sugar aware,” “Swap some sugar out,” and “Find a balance.” The Preteen app does not include stages, only aims and tasks.	1.1 Goal setting (behavior)
		1.5 Review behavior goal(s)
		1.7 Review outcome goal(s)
Task *PT, T, P*	Stages consist of a number of tasks that break the aim and stage down into small, achievable tasks. For example, the stage “Swap some sugar out” contains tasks such as replacing sugary drinks with water, reading a specific article in the app, reading labels to identify sugary foods in the home, and making a list of snacks eaten and circling those that are high in sugar.	1.2 Problem solving
		1.4 Action planning
		4.1 Instruction on how to perform a behavior
		4.2 Information about antecedents
		7.1 Prompt/cues
		8.1 Behavioral practice/rehearsal
		8.2 Behavior substitution
		8.3 Habit formation
		8.4 Habit reversal
		8.7 Graded tasks
		10.4 Social reward
		13.2 Framing/reframing
Check-In *PT, T, P*	At any time, users can access and update their health behavior status. The Check-In area provides a graph-formatted overview of how they are doing in terms of six self-rated health behaviors: sugary drinks, veggies and fruit, activity, family meals, screen time, and sleep. Each behavior has a short description of the health behavior recommendation, and users are asked to rate how they think they’re doing on a scale from poorly to not very well to okay to well to great.	2.2 Feedback on behaviors
		2.3 Self-monitoring of behaviors
		2.4 Self-monitoring of outcome(s) of behavior
Discover *PT, T, P*	Articles are an in-app resource for users who wish to learn more about particular topics. The Discover Center allows users to explore educational content at their own pace. Content is organized by health behavior topic and takes the form of relevant health articles that users can consume quickly and refer back to over time. Users are prompted to provide a short written response to a question related to the article content (e.g., “What is your biggest challenge in sticking to a healthy breakfast routine?”). They are provided with currency when they respond. Users are also prompted to indicate the value they derived from articles; user ratings are combined to indicate popular articles.	4.1 Instruction on how to perform a behavior
		4.2 Information about antecedents
		5.1 Information about health consequences
		5.3 Information about social and environmental consequences
		5.6 Information about emotional consequences
		7.1 Prompts/cues
Environmental components		
Social Wall *PT, T, P*	The Social Wall offers a safe social space within the application where users can come together and share thoughts, feelings, successes, and challenges around their healthy lifestyle goals. Prompts guide behavior change through feeling connected, listening, having a voice, and shifting norms. Humans are social creatures and our social networks play a huge part in our lives. Social networks have been shown to influence health outcomes like weight and medication adherence. This is especially true if the health issue has stigma surrounding it. When uncertainty is high, users are more influenced by their peers. Offering a safe social space where users can come together around common health goals is therefore considered imperative for long-term success. Self-efficacy, the most important influence on behavior change, is boosted by having access to a social space that is promoting healthy behaviors. The social wall will be moderated by the health coach and has some automated moderation built in to hold posts with inappropriate language. The moderator can review and approve the held posts; otherwise, posts go live immediately.	3.1 Social support (unspecified)
		3.2 Social support (practical)
		3.3 Social support (emotional)
		6.1 Demonstration of behaviors
		6.2 Social comparison
		13.1 Identification of self as role model
Virtual Coach *PT, T, P*	The Virtual Coach, Aimbot, is a digital bot with a range of pre-programmed prompts, questions, and answers designed to guide users in the app with behavior change in an empathetic way. All app users can access Aimbot. The content is based on queries that arose during the pilot.	3.2 Social support (practical)
Health coach *PT, T, P*	The health coach, trained in motivational interviewing, provides support to app users through an in-app coaching interface in which the Coach and user can have one-on-one messaging conversations to provide more tailored and more personal health behavior guidance.	2.2 Feedback on behavior
		3.1 Social support (unspecified)
		3.2 Social support (practical)
		3.3 Social support (emotional)
		10.4 Social reward
Parent Companion App *P*	The Parent Aim2Be Companion App complements the child’s Aim2Be app. It includes many of the same components (Quick Wins, Aims, Stages, Tasks, Health Behavior Check-Ins, Articles, Social Wall, Virtual Coach, health coach) and similar nutrition, activity, screen time, and sleep related content, but focuses primarily on how parents can support their children in making healthy behavior changes. The child and parent apps are not connected. The parent app is not gamified.	3.1 Social support (unspecified)
		3.2 Social support (practical)
		3.3 Social support (emotional)
		12.1 Restructuring physical and social environment

PT = Preteens; T = Teens, P=Parents

### Study conditions

Intervention condition participants will have access to the full version of the Aim2Be app (as described in Table 1) for 6 months. In addition, participants (teens and parents) will have the option to access a health coach who can support them in health behavior change using motivational interviewing techniques. The health coach has training in motivational interviewing and expertise in lifestyle management and working with families. The health coach will communicate with participants through the in-app text feature, and participants have the option to schedule a live text session if they wish to do so. The health coach will send an initial contact to all participants and will send follow-up supportive messages. The exact messaging and frequency of messaging that the health coach will provide to participants cannot be predicted, as this coaching will be individually tailored to the questions and concerns participants raise with the health coach, and the frequency with which they reach out to the health coach. This is in line with the autonomy support model featured throughout Aim2Be, where participants can choose the health behaviors on which they wish to focus.

Waitlist control condition participants will be put on a waitlist for 3 months during which time they receive a brochure with Canadian health recommendations about physical activity, diet, screen time, and sleep habits (this represents the duration in which they are part of the efficacy trial—see Fig. 1). Once their 3-month assessment is complete, they will have access to Aim2Be app, with no health coach, for the following 3 months. Participants will have access to all features of the Aim2Be app except the health coach and will be assessed 3 months after they were given access to the Aim2App with no health coach. This 3-month period will be compared to the 3-month period of the intervention condition to determine differences in adherence in Aim2Be with and without health coach support.

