## Methods/Design

### Study design

Two hundred Canadian children who have overweight or obesity and one parent for each will participate in the trial, which is taking place in 2019–2020. Most participants will be recruited for a study funded in part by the Public Health Agency of Canada with matched funds from partners. A portion of the participants (*n* = 60) will be recruited as part of a study embedded within a Canadian Institutes of Health Research (CIHR) Team Grant in Bariatric Care (Team ABC 3) [27]. After consent and baseline measurements, families will be randomized into one of two conditions: 1) intervention or 2) waitlist control. Families randomized into the intervention condition will receive the Aim2Be app with health coaching (i.e., receive tailored messages from a health coach with the option of scheduled and unscheduled text support). All participants will receive a package containing a scale, measuring tape, activity tracker (Fitbit), and a brochure with current health recommendations. At 3 months, families randomized to the waitlist control conditions will move to the intervention for months 3 to 6, but they will not be supported by the health coach. Data collection will occur at baseline, 3 months, and 6 months, utilizing REDCap (Research Electronic Data Capture) [28, 29] hosted at BC Children’s Hospital Research Institute (BCCHRI). Staff involved in the data collection and analysis will not be involved in delivering the intervention. Ayogo Health Inc. and the Childhood Obesity Foundation (COF) will deliver the Aim2Be intervention. The BCCHRI/School of Population of Public Health (SPPH) at the University of British Columbia (UBC) will collect and analyze the data. The study flow chart is shown in Fig. 1.

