### Sample size calculation

Based on previously published data [31], the RCT will have 80% power at an alpha of .05 to detect a .5 decrease in BMI z-score when the sample size in each group is 60. The BMI z-score was used to calculate sample size because this is the most difficult variable to change and requires the largest sample size of all of the primary outcomes. Based on this and accounting for both missing data and attrition, we project needing at least 80 families in each condition. However, to be able to detect a 20% difference in adherence (e.g., secondary aims outcome) between the two intervention groups (odds ratio of 2.33) at an alpha of .05 with 80% power using a one-sided t-test, 77 families are needed in each group. As the waitlist control group will receive the intervention at 3 months, we require 100 participants enrolled in each group (this accounts for 15% attrition from baseline to 3-month and the approximately 8% of families who will not download the Aim2Be app). Power calculations were conducted in nQuery (Statsols, USA). Based on these computations, we aim to enroll 200 participants in the RCT.

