## Trial status

The trial is scheduled to be completed by November 30, 2020. Recruitment began on January 2, 2019, and will be completed by approximately October 31, 2019.

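### The adherence comparison credits the health coach with a difference that also contains a 3-month delay in access and, if only waitlist starters are analysed, retention to month 3

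*Protocol article*

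**What the plan says.** All references are to the protocol article.

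- **Access, intervention arm** (Study conditions): "Intervention condition participants will have access to the full version of the Aim2Be app (as described in Table 1) for 6 months". Coaching is available from the start.
- **Access, waitlist arm** (Study design): "families randomized to the waitlist control conditions will move to the intervention for months 3 to 6". Study conditions adds: "Once their 3-month assessment is complete, they will have access to Aim2Be app, with no health coach, for the following 3 months".
- **The contrast** (Study conditions), speaking of the waitlist arm's months on the app: "This 3-month period will be compared to the 3-month period of the intervention condition to determine differences in adherence". The sentence goes on to read the difference as one between having and not having the coach, which is secondary aim 1.
- **Sample size** (Sample size calculation): the target is a 20% difference in adherence with an odds ratio of 2.33, and "at an alpha of .05 with 80% power using a one-sided t-test, 77 families are needed in each group". Enrolment is set at 100 per group; "this accounts for 15% attrition from baseline to 3-month and the approximately 8% of families who will not download the Aim2Be app".
- **Analysis** (Statistical analyses): linear regressions of time in the app, days of use and tasks completed, transformed for skewness. No term for time of access or calendar date is mentioned for this comparison. Multiple imputation is named in general terms.
- **Calendar** (Trial status): "Recruitment began on January 2, 2019, and will be completed by approximately October 31, 2019".
- **Limitations** (Discussion): the short intervention period is named. The timing of access in the adherence comparison is not.

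**The concern.** Randomisation decides two things at once: whether a family has a coach, and when it gets the app. Every uncoached user has waited about three months, already holding the Fitbit, scale and brochure. No coached user has waited. Any effect of the wait on app use, in either direction, therefore appears in the result as an effect of the coach.

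A second difference comes from attrition. Families lost before month 3 never reach the app in the waitlist arm. Their counterparts in the intervention arm are offered it at baseline, and the app records their use whether or not they later complete a survey. Comparing all intervention families with waitlist starters then compares a whole arm with a selected one. Restricting the intervention arm to 3-month completers does not repair this, because coaching may itself affect who completes.

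At stake is the reading of secondary aim 1, which also sets the size of the trial. Efficacy needs at least 80 families per arm and adherence raises this to 100, so 2 × (100 − 80) = 40 further families are enrolled for this comparison.

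**Working it through.** **1. The plan's own figures.** For two proportions, one-sided alpha 0.05, 80% power and pooled variance under the null:

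n = [1.645·√(2p̄(1−p̄)) + 0.842·√(p₁(1−p₁)+p₂(1−p₂))]² / (p₁−p₂)²

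- 40% v 60% (odds ratio 2.25): n = 77, the stated number.
- 50% v 70% (odds ratio 2.33): n = 74; power at 77 is 81.8%.
- Enrolment: 77/(1 − 0.15 − 0.08) = 77/0.77 = 100.

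The arithmetic is sound. Attrition enters it only as a loss of numbers.

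**2. Who is compared.** Per 100 randomised, with the plan's rates and 8% non-download assumed in both arms:

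| | Intervention | Waitlist |
|---|---|---|
| Offered the app | 100, at baseline | 100 × 0.85 = 85, at month 3 |
| Download it | 100 × 0.92 = 92 | 85 × 0.92 ≈ 78 |
| Coach | yes | no |
| Wait before access | none | about 3 months |

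Coach and wait coincide exactly. No regression term can separate them, because no family is coached after a wait or uncoached without one.

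**3. Selection alone (assumed rates).** Suppose the coach has no effect, a share p of retained families adheres, and a share q of families lost by month 3 adheres. The intervention arm averages 0.85p + 0.15q and the waitlist starters p, so the spurious difference is 0.15(q − p).

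- p = 60%, q = 20%: 51 + 3 = 54% v 60%, or −6 points (30% of the 20-point target).
- p = 60%, q = 40%: 51 + 6 = 57% v 60%, or −3 points.
- p from 50% to 70%, q from 0% to 50%: 0 to −10.5 points.

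**4. What a bias does to the test.** With 78 per arm, 50% in the waitlist arm and a one-sided 5% test:

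| Bias (points) | Rejection, no coach effect | Rejection, true 20-point effect |
|---|---|---|
| −10 | 0.2% | 35% |
| −5 | 1.2% | 60% |
| 0 | 5% | 82% |
| +5 | 15% | 95% |
| +10 | 35% | 99% |

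Negative values stand for selection in favour of waitlist starters; positive values for higher use among immediate starters for reasons other than the coach. Both sets are assumptions.

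**5. Calendar.** If randomisation follows recruitment closely, intervention families start from January to October 2019 and waitlist families from about April 2019 to January 2020. Start dates overlap from April to October, 7 of the 10 months, so season is partly confounded and can be partly adjusted for.

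**The case against.** The strongest reply is that randomisation is not lost. Immediate access with a coach against delayed access without one is a randomised contrast, and it stays valid if all families are analysed. Nothing in the article says that only starters or completers will be analysed. Multiple imputation is planned, and an article may leave the analysis set to the full plan. This stands, which is why the retention point is conditional. It does not rescue the attribution to the coach: the delay is built into the design and no analysis set removes it.

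Several stronger readings are tempting and are not supported:

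- **That finishing the 3-month assessment is a strict condition of access.** Study conditions can be read so, but Study design gives only the timing. The planned 15% attrition still implies that some waitlist families never start.
- **That the intervention arm's window is undefined.** Its first three months are the natural reading, although the text names no months for an arm with six months of access.
- **That season is wholly confounded.** Step 5 shows the overlap.
- **That the bias is known to be large.** The rates are assumed, and they treat adherence as binary, whereas the plan analyses transformed continuous measures.

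It is also fair that the aim is secondary and declared exploratory, without a hypothesis.

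**Conclusion.** The concern holds in a limited form. Followed as written, the plan would report as a coaching effect a difference that also contains a three-month delay in access. If only waitlist families who start the app are analysed, it would contain selection by retention as well. Calendar time is a partial confounder.

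The net direction and size cannot be told from the documents. Selection of retained families would favour the waitlist arm; the wait could act either way. The 3 to 6 points against a 20-point target illustrate selection only, and rest on assumed adherence of 60% in retained families and 20% to 40% in those lost.

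A reader might infer that the adherence data are worthless or that the trial is compromised. Neither follows: the comparison can still answer the narrower question of immediate coached against delayed uncoached access, and the primary 3-month efficacy comparison is unaffected.

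**What to change.** Before results are seen:

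1. State the window as the first three months after access in both arms, that is, months 0 to 3 for the intervention arm.
2. Weight waitlist starters by the inverse probability of reaching access, modelled on baseline data, so that they stand for all randomised waitlist families. Say that this corrects only selection explained by the measured variables.
3. Adjust for calendar month of access start. Outside April to October 2019 this adjustment relies on the model.
4. Word the conclusion as immediate access with coach versus delayed access without coach. List the delay as a limitation and claim no effect of coaching alone.

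Counting never-started waitlist families as zero use should not be the sensitivity analysis, because it penalises families who were never offered the app. On the rates above with no coach effect, the waitlist arm becomes 0.85 × 60 + 0.15 × 0 = 51% against 54% to 57%, a spurious 3 to 6 points in favour of coaching.

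The cost is a little more analysis work and a weaker conclusion for a secondary aim. No new data are needed.
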